### Measures

The baseline assesses all socio-demographic and trait constructs that are not expected to change due to the manipulation in the laboratory part of the study. In the laboratory momentary physiological, affective, self-evaluative, and relationship variables are assessed. The post-manipulation physiological assessments and self-reports repeat some of these momentary states to capture the effects of the four experimental conditions. An overview of the measurement points in time and instruments can be found in the SPIRIT chart in Table 3.

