#### Need satisfaction through support provision

Based on the event-based scale to assess psychological needs satisfaction by certain events [79], a set of 9 items, translated into German, is used to measure the satisfaction of the basic needs of autonomy, competence and relatedness through the provision of social support with three items each. At baseline, the original instruction “During this event I felt…” was adapted to prompt participants to think of support situations “While providing support in the last month, I felt...”. Directly after the support manipulation in the laboratory, the questionnaire is used again with adapted instructions to measure basic need satisfaction during the experiment “During the task I just completed, I felt ...”. Participants respond on a scale from 1 (not at all) to 5 (very much).

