### Planned analyses

Analyses of variance and linear mixed models between conditions and pre- and post-assessments will be performed on self-reported self-evaluative and affective as well as, physiological data and relationship variables. Of particular interest will be changes in positive and negative affect and ratings of competence and relatedness depending on the condition.

Data from participants who do not complete the full manipulation (that drop-out before the post-assessment) or show suspicion (e.g., enter trick questions into the chat boxes in order to check, whether they chat with their partners) will be analysed separately in per protocol and intention-to-treat analyses. No outliers are expected in the self-report data. In the event that participants fail to comply with the inclusion criteria for cortisol assessment (no strenuous exercise, food, alcohol, tooth brushing, smoking, caffeine, or cortisol affecting medication prior to the experiment), their cortisol data may have to be excluded post-hoc. Women who take oral contraceptives are included in the sample. For physiological data (cortisol, heart rate, heart rate variability, blood pressure) we consider truncation at 2 SD from the sample mean if outliers occur. Missing data will be handled via Full Information Maximum Likelihood (FIML).

In exploratory qualitative content analyses, we will investigate type and amount of support messages written into the computer chat boxes by participants in the three support provision conditions.

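### Competence and relatedness have no momentary pre-manipulation rating, so they are better compared between conditions on the post-task rating, adjusted for baseline, than as pre/post changes

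*Protocol article*

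**What the plan says.** The Planned analyses section of the protocol article opens with the model: "Analyses of variance and linear mixed models between conditions and pre- and post-assessments will be performed". The next sentence names the targets: "Of particular interest will be changes in positive and negative affect and ratings of competence and relatedness depending on the condition".

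The section Need satisfaction through support provision describes two administrations of the nine-item scale (three items per need, answered 1 to 5). In the online baseline the stem is "While providing support in the last month, I felt". After the manipulation the scale "is used again with adapted instructions to measure basic need satisfaction during the experiment", with the stem "During the task I just completed, I felt". The text describes no administration in the laboratory before the manipulation.

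The Measures section gives the online survey a different role: "The baseline assesses all socio-demographic and trait constructs that are not expected to change due to the manipulation". Affect is handled differently. The Positive and Negative Affect Schedule is given before and after the manipulation, both times about the momentary state.

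**The concern.** A pre/post change is informative when both values answer the same question. For affect they do. For competence and relatedness the items are the same, but the time frame, the recipient and the activity differ: everyday support to anyone over a month, against one laboratory task. In the observation condition that task contains no support at all.

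The ratings matter because they show whether each feedback manipulation induced the need it targets, and because they are the mediators in H6. Two things are at stake. The first is precision: subtracting a recall rating that may be only weakly related to the task rating adds noise to the comparison of conditions. The second is interpretation: a time effect, or a change within one arm, could arise only because people rate a chat task differently from a month of ordinary support.

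**Working it through.** **Inputs.** From Sample size calculation: four groups, two measurements, eta-squared 0.02, N = 216 (54 per group), 95% power. From Randomization: individual allocation to the four conditions. Not in the document, so assumed: two-sided alpha 0.05, equal SDs for the two ratings, the correlation r between them (range shown), a 0.5 SD difference between two arms, and independent participants.

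**The plan's own figure.** For the time-by-condition interaction, lambda = f² × N × m / (1 − r) with m = 2, df = 3 and 212. With f² = 0.02/0.98 = 0.0204 and r = 0.5, lambda = 0.0204 × 216 × 2 / 0.5 = 17.6, and power is 95.2%. So N = 216 is reproduced with r = 0.5. (This uses f = 0.143, which is what eta-squared 0.02 gives. With the printed f = 0.17, N would be 156 at r = 0.5 and 212 at r = 0.3. That is a separate matter.)

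**Variance of the arm difference, relative to the post-task rating alone**
- Change score: 2(1 − r)
- Post-task rating only: 1
- Post-task rating with baseline as covariate: 1 − r²

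The first minus the third is 2(1 − r) − (1 − r²) = (1 − r)², which is never negative. With equal SDs the adjusted analysis is therefore at least as precise as the change score at every r. The change score loses to the post-only comparison only if r is below 0.5.

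**Two-arm power, 54 per arm, 0.5 SD difference.** The noncentrality for the post-only test is 0.5 × √(54/2) = 2.598. The other two analyses divide this by the square root of the relative variance.

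| r | Change score: noncentrality, power | Post only: power | Adjusted: noncentrality, power |
|---|---|---|---|
| 0 | 2.598/√2 = 1.837, 44% | 73% | 2.598, 73% |
| 0.2 | 2.598/√1.6 = 2.054, 53% | 73% | 2.598/√0.96 = 2.652, 75% |
| 0.3 | 2.598/√1.4 = 2.196, 59% | 73% | 2.598/√0.91 = 2.724, 77% |
| 0.5 | 2.598/√1 = 2.598, 73% | 73% | 2.598/√0.75 = 3.000, 84% |

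**Four-arm test at N = 216**, with the post-rating effect held at the size that gives 95% power at r = 0.5. The change score has 69%, 80%, 85% and 95% power at r = 0, 0.2, 0.3 and 0.5. The adjusted analysis has 95%, 96%, 97% and 99%.

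**Validity of the condition-by-time contrast.** In 5,000 simulated trials per setting, with a constant shift of −0.8 SD between the two questions, this test rejected in about 5% of trials when no condition differed. With a true difference of 0.660 SD it recovered 0.655 to 0.658. The shift is common to all randomised arms and cancels.

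**Within-arm change.** Here the shift does not cancel. The expected change in an arm is the shift between questions plus any effect of the task, and the two cannot be separated.

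**The case against.** The strongest reply is that no sentence plans to subtract the last-month score. The key sentence can be parsed as changes in affect, plus ratings of competence and relatedness compared by condition. The article lists the online baseline separately from the assessment directly before the manipulation, so the pre/post pair may mean the laboratory assessments only, and then there is nothing to subtract for this scale. The Measures section treats the online survey as holding traits. The schedule in Table 3 is not shown, so a further laboratory rating cannot be strictly excluded.

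This stands as far as it goes: the subtraction is an inference. It does not remove the point. Both readings follow directly on a pre/post model sentence, the wording permits the change analysis, and the proposed analysis is at least as good under either reading.

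Three stronger readings are tempting and are not supported.
- A reader might infer that the planned test says nothing about the manipulation. The wording points to a comparison between conditions, and under randomisation that comparison is valid.
- A reader might expect a high false-positive rate. At r = 0.2, a within-arm paired test would reject in 21%, 40% and 81% of trials for assumed shifts of 0.2, 0.3 and 0.5 SD with no manipulation effect. No passage names such a test on this scale. H1 concerns physiological, affective, self-evaluative and relational responses in all conditions and does not name the need ratings. The figures apply only if such a test were run.
- A reader might think the mediation hypothesis is affected. H6 already uses self-reports during the manipulation.

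It is also fair to say that the power loss depends on a correlation the article does not give, and that the same nine items answered by the same person could correlate moderately.

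**Conclusion.** The concern holds in a limited form. The text describes no momentary pre-manipulation value for competence and relatedness, yet the wording most naturally places these ratings in a pre/post change analysis.

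The consequence for the comparison of conditions is lost efficiency and not bias. Over the assumed correlations the shortfall against the adjusted analysis runs from 73 − 44 = 29 points at r = 0 to 84 − 73 = 11 points at r = 0.5. This rests on equal SDs, independent participants and a 0.5 SD difference. Against an unadjusted post-task comparison there is no loss at r = 0.5, and the change score gains above it.

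The consequence for a time main effect or within-arm change is one of meaning: on this scale neither can be attributed to the manipulation.

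**What to change.** In Planned analyses, keep the change wording for positive and negative affect. For competence and relatedness, state that the post-task rating will be compared between conditions with the last-month need-satisfaction score as a covariate, and that no time main effect or within-arm change on this scale will be interpreted. H6 needs no change.

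The cost is one or two sentences and no new data, since both ratings are already collected. The one thing given up is a within-arm change in need satisfaction, which the two differently worded questions cannot support.

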**Methods:**

A priori power analyses resulted in a planned sample size of 250 participants randomized to four conditions: 1) no support provision, 2) support provision without feedback, 3) support provision with feedback on competence, 4) support provision with feedback on relatedness. Primary outcomes are immediate physiological (saliva cortisol, heart rate, heart rate variability, blood pressure), affective (positive and negative affect, anxiety), self-evaluative (e.g., self-esteem) and relationship outcomes. Generalized linear models will be used to compare the four conditions.

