### Sample size calculation

Meta-analyses summarizing effects of experimental manipulations of prosocial behaviour on well-being resulted in small- to medium-pooled effects sizes from Cohen’s d = .28 [33] to Pearson’s r = .32 (corresponding to a Cohen’s d = .68; 43). Whereas these effect sizes represent support provision vs. no support provision, we are particularly interested in manipulating and comparing the effects of different conditions under which support is provided. Therefore, we base our power analyses on a small n^2^ of 0.02 for the interaction term of time*condition (Cohen, 1992; effect size f = 0.17). We deem a power of 95% desirable to detect effects not only between the ‘support’ to ‘no support’ group, but also between the groups that provide support under different conditions. With 4 between- and 2 within-subject factors entered into a repeated measures ANOVA, G*power estimates a total *N* = 216 (54 per group) to result in a 95% chance to reject the null hypothesis of no significant interaction term [66]. To allow for attrition due to failed manipulation (e.g., participants provide no support despite randomized to chosen support groups), we plan to recruit 250 participants randomized to four groups (125 dyads).

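### ANOVA and linear mixed models are planned for the same outcomes with neither named as decisive, and the FIML promise fits only the mixed models

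*Protocol article*

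**What the plan says.** Four statements in the protocol article bear on how the conditions will be compared.

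- **Planned analyses, models:** "Analyses of variance and linear mixed models between conditions and pre- and post-assessments will be performed". The sentence covers self-evaluative, affective, physiological and relationship outcomes together. It does not assign either method to particular outcomes or hypotheses.
- **Planned analyses, missing data:** "Missing data will be handled via Full Information Maximum Likelihood (FIML"). The sentence is not limited to one of the two methods.
- **Abstract, Methods:** "Generalized linear models will be used to compare the four conditions".
- **Sample size calculation:** "With 4 between- and 2 within-subject factors entered into a repeated measures ANOVA", the required total is 216 (54 per group). Recruitment is set at 250 people in 125 dyads, and the surplus is meant for attrition from failed manipulation.

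Planned analyses also foresees people who leave before the post-assessment, and cortisol data that may have to be removed afterwards. No expected rate is given for either.

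**The concern.** Repeated measures ANOVA and a linear mixed model can give much the same answer when every participant has every value. They part company when values are missing. The usual least-squares ANOVA has no likelihood into which an incomplete record can enter, so in practice it keeps complete cases. A mixed model fitted by maximum likelihood uses whatever each participant supplied. The FIML sentence therefore describes one of the two named methods and not the other.

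Two things are at stake.

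1. **Which result counts.** For an outcome measured more than once, H3 to H5 could each be answered twice, on different sets of participants and with different p-values. If the two disagree, nothing in the article says which one settles the hypothesis.
2. **Who is analysed.** If missing values are related to stress or to condition, a complete-case ANOVA can be selective where the likelihood-based model is less so, provided missingness depends only on observed data.

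The conventional ANOVA also treats the two members of a dyad as independent. Ignoring that pairing could misstate standard errors. How far, and in which direction, depends on the within-dyad correlation and on how often partners share a condition; the article gives neither.

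**Working it through.** **Step 1. The statements side by side**

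| Place | Model named | Can it use FIML? |
|---|---|---|
| Abstract, Methods | Generalized linear models | Depends on the specification, which is not given |
| Sample size calculation | Repeated measures ANOVA | Not as conventionally fitted by least squares |
| Planned analyses | Analyses of variance | Not as conventionally fitted by least squares |
| Planned analyses | Linear mixed models | Yes, if fitted by maximum likelihood |

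The missing-data promise has a home in the last row only. No row is marked as decisive.

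**Step 2. Reproducing N = 216**

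- From Sample size calculation: eta squared 0.02 for time by condition, power 95%, 4 groups (k = 4). The within-subject part is read as 2 measurements (m = 2).
- Assumed, because not stated: alpha = 0.05 and correlation between measurements rho = 0.5.
- f = sqrt(0.02 / 0.98) = 0.1429.
- Noncentrality = N f² m / (1 − rho) = 216 × 0.020408 × 2 / 0.5 = 17.63, with df1 = (k − 1)(m − 1) = 3 and df2 = (N − k)(m − 1) = 212.
- Power = 95.2%, and 216 is the smallest multiple of four that reaches 95%.

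The figure reproduces for **two** measurements. The printed "effect size f = 0.17" would give 156 under the same settings. That mismatch with eta squared 0.02 is a separate matter and does not affect this point.

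**Step 3. The margin**

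250 − 216 = 34 people, and 34 / 250 = 13.6%.

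**Step 4. Complete cases under assumed missingness**

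The article gives no rate, so p per measurement is an assumption, taken as independent across measurements. For two measurements, complete cases = 250 × (1 − p)².

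| p per measurement | Complete cases | Power at that N (f = 0.1429) |
|---|---|---|
| 2% | 240.1 | 97.0% |
| 3% | 235.2 | 96.7% |
| 5% | 225.6 | 96.0% |
| 7% | 216.2 | 95.2% |
| 10% | 202.5 | 93.7% |

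Break-even with 216 is p = 1 − sqrt(216 / 250) = 7.0%. A total loss of 20% (N = 200) would leave 93.4% power.

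**Step 5. Why six cortisol samples should not be set against 216**

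The saliva cortisol section speaks of five samples and lists six time points. With six, 250 × (1 − p)⁶ gives 221.5, 208.2 and 183.8 at 2%, 3% and 5%. But 216 is not the requirement for six measurements. With the formula and assumptions of Step 2, plus sphericity, m = 6 needs N = 120, and N = 184 has about 99.8% power. The lower counts show no shortfall in power.

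**The case against.** The strongest case on the other side has four parts.

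1. **The methods may divide by outcome.** Several measures refer to the task just completed or to its effect, such as the state change items, the evaluation of support and the empathic reaction. A between-condition ANOVA for those and mixed models for repeated outcomes is a natural reading. It stands as a possibility, but the article does not say so: its sentence applies both methods to all outcome families and to pre- and post-assessments.
2. **FIML does have a planned home.** The mixed models named in the same section can deliver it. This stands, and it is why a reader who infers that the analyses contradict each other goes too far. They are inconsistent and unranked, not mutually exclusive.
3. **The abstract uses an umbrella term.** ANOVA and ordinary linear models are special cases of the generalized linear model, and the swap item is binary. The abstract is loose rather than wrong, though it still does not name the mixed model.
4. **Which model decides is detail for an analysis plan.** An article may leave such detail out. This one, however, states its models, does so differently in three places, and attaches to all of them a missing-data method that one cannot use.

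A reader might also infer that the plan discards everyone with a missing time point, or that the analysed number will fall below 216. The documents support neither. Complete-case analysis is the usual behaviour of the method, not something the article states. No missing-data rate is given, and 216 belongs to two measurements, where 2% to 5% missing leaves it intact. One qualification remains: the 34 spare participants were set aside for failed manipulation, so ordinary missing data would draw on the same margin.

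**Conclusion.** The point holds as one of unclear and mismatched analysis choice. For outcomes measured more than once, the article plans two methods that treat missing values differently, names neither as decisive, and states a missing-data approach that only the mixed model can honour. The ANOVA that carries the sample size also leaves the 125 dyads out of account.

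The effect on power cannot be fixed from the article and is probably small. Under the settings that reproduce 216 (alpha 0.05, rho 0.5 and f = 0.1429), 5% missing at each of two measurements leaves 96.0% power, and a 20% overall loss leaves 93.4% against the intended 95%. These figures assume independent missingness and independent participants. The case for change rests on removing the choice between two results and on using all available data, not on a shortfall in numbers.

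**What to change.** - **Continuous outcomes measured more than once:** make one linear mixed model the confirmatory analysis, with condition by time, random intercepts for participant and dyad, and maximum likelihood on all available data. Enter the pre-manipulation value either as a time level or as a covariate, not both. As a covariate, it would exclude anyone who lacks it.
- **Continuous outcomes measured only once, after the manipulation:** compare conditions with a model that has a dyad random intercept.
- **The yes/no item on replacing the partner:** use a logistic model.
- **Missing data:** state that FIML refers to the likelihood of these models.
- **ANOVA:** delete it from Planned analyses or label it supportive.
- **Abstract:** replace the generalized linear model wording so that it matches.

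The cost is low. Mixed models are already planned and no new data are needed. Beyond the wording, the team must list which outcomes are repeated and which are measured once, and add the dyad effect. Data collection was still ongoing according to Data Availability, so the choice can be recorded before the conditions are compared.

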## Discussion

The current research evidence suggests that individuals who engage in prosocial behaviour tend to report higher levels of subjective well-being [33, 43, 136], greater life satisfaction [137], and a reduced mortality risk [8] among other benefits. Conversely, research has repeatedly demonstrated that, for instance, caregiving can result in burnout and health limitations. The new experimental paradigm described in this protocol, bases on self-determination theory [50], and employs a controlled experimental design to manipulate the conditions of providing social support in a laboratory setting to assess its impact on a range of outcomes, including physiological, affective, self-evaluative, and relationship indicators in dyads.

The objective of the paradigm is to examine the circumstances under which providing social support (via chat messages) to a close social network member (in another room) has beneficial effects for the provider. The observation condition serves as the control condition, in which participants are presented with an alleged stress and pain response by their partner person (on a computer screen), who allegedly endures stress tasks in another room. This observation condition is compared to a condition in which participants are given the opportunity to send supportive chat messages to their allegedly stressed partner person, without receiving any feedback on their supportive efforts (support provision only condition). In order to manipulate perceptions of competence in providers, the third condition (support provision with feedback on competence condition) manipulates partner persons' stress responses shown to providers in a way that after each supportive message a decrease in partner persons’ stress response is shown. The fourth condition manipulates perceived relatedness by showing hugging icons, allegedly sent by the partner person, in response to supportive messages by the provider (support provision with feedback on relatedness condition). The third basic psychological need, autonomy, was not manipulated. However, in each support provision condition, it was highlighted that writing supportive messages is voluntary.

By considering the beneficial effects on relatedness and competence, in addition to autonomy, our study aims to investigate basic psychological processes set into motion by providing social support. This basic knowledge might be used to explain more applied phenomena in everyday support provision. For example, prolonged caregiving for chronically or terminally ill patients has displayed serious detrimental effects but simultaneously beneficial effects on caregivers’ health and longevity [17]. Whereas studies that show detrimental effects of caregiving rely on self-reports from care providers regarding the amount of caregiving [138, 139], the surprisingly positive effect of caregiving on longevity by Brown et al. [17] is based on hours of care *reported by recipients*. Caregivers often feel *obliged* to care for loved ones and give prolonged care they *perceive* as ineffective, resulting in higher levels of stress [39, 140]. Nevertheless, if the level of care provided is acknowledged by the recipient, the efforts of the caregiver may still facilitate the formation of a sense of relatedness [141]. This way, appreciation by recipients may help turn even obligatory, less effective support provision into opportunities to fulfil the basic psychological need for relatedness. As discerning the underlying condition of such complex processes in everyday life is challenging, our paradigm provides a means of manipulating feedback for support provision in a controlled laboratory setting. The results of the described experimental approach will be of particular value when synthesized with measurements taken under natural conditions in the ecological assessment design of the same project (Study 3 and 4, see OSF: https://osf.io/8spzw). This will provide insights into how helping behaviours may impact the helpers themselves, either positively or negatively. Furthermore, these findings can provide insight into how supporting others can have detrimental or beneficial effects on the providers of support. They can also indicate whether the benefits of support provision depend on the satisfaction of basic motivational needs. This can inform the development of preventive and interventional approaches in various areas of life, including romantic and peer relationships (e.g., help acknowledgment in partnerships, support provided to co-workers), motivational and developmental research over the life-span (e.g., prevention of caregiver burnout, volunteering in middle age and active aging, motives for helping), and the applied clinical context (e.g. therapeutic relations and interventions).
